**Analysis plan**

Study 1 Descriptive analysis of baseline profile of participant demographics (age, gender, economic status) will be presented.

Non-parametric correlations and paired sample t-tests will be conducted to examine and analyse changes in primary outcome (dementia awareness, brain health risk profile) at baseline to three months.

**Study 2** Interview data will be analysed qualitatively for content and themes that emerge, and coded and categorised using N Vivo software

**Study 3** Descriptive statistics will be calculated for participant demographics and domains of the virtual reality screener and the traditional cognitive assessments. This will include percentage of participants who successfully completed the virtual reality cognitive assessments, time taken to complete the virtual reality cognitive assessment module, and scores from the feedback questionnaire.

Correlational analyses and receiver operating curve (ROC) will be conducted for performance scores on the virtual reality assessment module and scores on other cognitive assessment tests.

Duration of the Study 24 months

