# 2. HYPOTHESIS

Our hypotheses are that:

1. The Brain Bootcamp campaign will improve older adults’ brain health risk profile at follow-up assessment.
2. The Brain Bootcamp campaign will increase older adults’ dementia awareness and knowledge of modifiable risk factors.
3. The virtual reality cognitive screener is feasible and acceptable for use with younger and older adults.
4. The virtual reality cognitive screener is able to discriminate between cognitively intact and cognitively impaired participants.

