# 3. STUDY OBJECTIVES

**Study 1**

### 3.1. STUDY 1 PRIMARY OBJECTIVES

(i) To evaluate the impact of the Brain Bootcamp campaign in increasing dementia awareness and knowledge of modifiable lifestyle factors in older Australians

(ii) To evaluate the impact of the brain bootcamp campaign in improving older adults’ brain health risk profile

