**Table 2. Assessment measures for participants**

| Study 1 | | |
| --- | --- | --- |
| Outcome | Data collection instrument | |
| Primary Outcomes | | |
| Dementia Awareness | Dementia Awareness Questionnaire [22, 23] | |
| Brain health risk profile | LIBRA index [19] | |
| Motivation | Motivation to Change Lifestyle and Health Behaviour for Dementia Risk Reduction (MCLHB-DRR)[24] | |
| Quality of life | EuroQol Group EQ-5D-5L [25] | |
| Social networks | Lubben Social Network Scale (LSNS-6) [26] | |
| Overall experience | Impact Evaluation survey [27] | |
|  |  |  |
| Study 2 | | |
| Outcomes | | |
| Behaviour change/ impact of campaign | Semi-structured interviews | |
| Study 3 | | |
| Outcomes | | |
| Memory performance | Virtual reality assessment (developed in house by our researchers)  Telephone Interview for Cognitive Status-Modified (TICS-M) | |
| Acceptability | Research-team generated feedback survey | |

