### 8.2. PROVIDE A DETAILED ANALYSIS PLAN

**Study 1**

All surveys will be visually inspected for completeness on collection to minimise missing data. Assessment data will be entered into databases and analysed using standard statistical software (eg. SPSS V.22). Quantitative data obtained in response to structured assessment items will be entered, cleaned, analysed and summarised. The investigators will use descriptive statistics to describe the study group and to summarise their use of various components of the Brain Bootcamp Pack over the course of three months. Paired sample t tests will be used to analyse changes in our primary outcome, brain health risk profile, from baseline to three months. Nonparametric correlations will be conducted to examine the relationship between secondary outcomes (social networks, quality of life, motivation and dementia awareness) and changes in primary outcome.

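### The protocol contradicts itself on Study 1's primary outcomes: the Summary plans a paired test of change in dementia awareness, while section 8.2 makes awareness secondary and only correlates it with change in risk profile

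*Protocol*

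**What the plan says.** Four places in the protocol bear on the rank and analysis of dementia awareness in Study 1.

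- **Objectives and hypotheses.** Section 3.1 lists two primary objectives. The first is "To evaluate the impact of the Brain Bootcamp campaign in increasing dementia awareness and knowledge of modifiable lifestyle factors in older Australians"; the second concerns the risk profile. Hypothesis 2 in section 2 predicts an increase in "dementia awareness and knowledge of modifiable risk factors".
- **Summary, Analysis plan.** "Non-parametric correlations and paired sample t-tests will be conducted to examine and analyse changes in primary outcome (dementia awareness, brain health risk profile"), from baseline to three months. This makes two primary outcomes, with a paired comparison planned for both.
- **Section 7, Table 2.** The only outcome heading for Study 1 is "Primary Outcomes". Six rows follow it: dementia awareness, brain health risk profile (LIBRA), motivation, quality of life, social networks and overall experience.
- **Section 8.2, Study 1.** "Paired sample t tests will be used to analyse changes in our primary outcome, brain health risk profile, from baseline to three months". Nonparametric correlations are then planned for "the relationship between secondary outcomes (social networks, quality of life, motivation and dementia awareness) and changes in primary outcome".

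Section 8.1 sizes Study 1 on the dementia risk score alone. Section 7 defines an improvement in dementia literacy as one to three standard deviations relative to baseline, but section 8.2 does not use that definition.

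**The concern.** The two statements of the analysis disagree on whether a primary objective receives a test. Under the Summary, awareness is primary and its change is tested. Under section 8.2, awareness is secondary and enters only as a correlate of change in another outcome. Nothing in the protocol says which statement governs.

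Section 8.2 is the detailed plan, so an analyst would naturally follow it. The study could then end without an effect estimate, interval or test for the question listed first among its primary objectives. The choice between one and two primary outcomes, or six if Table 2 is read literally, would also be left to whoever writes the analysis. If that happened after the data were seen, the choice could follow the results.

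**Working it through.** **1. The passages side by side**

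| Place | Outcomes treated as primary | Analysis of awareness |
| --- | --- | --- |
| Section 3.1 | 2, through the primary objectives | not stated there |
| Summary, Analysis plan | 2 (awareness, risk profile) | paired t-test of change, and nonparametric correlations |
| Section 7, Table 2 (as extracted) | 6 | not stated there |
| Section 8.2 | 1 (risk profile) | correlation with change in risk profile only |

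The conflict between the Summary and section 8.2 is in running text, so it does not depend on how the table was extracted.

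**2. Can the section 8.2 correlation answer objective (i)?**

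Objective (i) and hypothesis 2 concern a rise in awareness, that is, whether the mean of (follow-up minus baseline) exceeds zero. Section 8.2 does not say whether awareness enters the correlation as its baseline value, its follow-up value or its change. The answer is the same in each case:

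- *Follow-up value or change.* Add a constant c to every participant's follow-up score. The ranks do not move, so a rank correlation with LIBRA change is identical whether c is zero or large.
- *Baseline value.* The follow-up awareness score does not enter at all.
- *Extreme case.* If everyone gains the same amount, the change has no variance and the correlation is undefined, although awareness has risen in every participant. Conversely, a strong correlation can occur with a mean gain of zero.

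The planned coefficient therefore carries no information on whether mean awareness rose.

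**3. Error rate and cost if both outcomes stay primary**

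Inputs: planned enrolment of 500 (Summary and section 4.2); 25% dropout, 90% power and α = 0.05 (section 8.1). Two-sided tests are assumed, since sidedness is not stated.

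- Family-wise error for two independent unadjusted tests: 1 − 0.95² = 0.0975, or 9.8%.
- Completers: 500 × 0.75 = 375.
- Detectable change, in SD of the change, by normal approximation: d = (z for α + z for power) / √n.
  - At 0.05: (1.960 + 1.282) / √375 = 3.242 / 19.36 = 0.167; the noncentral t gives 0.168.
  - At 0.025: (2.241 + 1.282) / √375 = 3.523 / 19.36 = 0.182; the noncentral t gives 0.183.
- Range: if only the 403 of section 8.1 were enrolled, completers would be 403 × 0.75 ≈ 302. The noncentral t values become 0.187 and 0.204.

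The derivation of 403 is a separate matter, and nothing here depends on it.

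**The case against.** The strongest objection is that the protocol does plan a test of awareness. The Summary names it as a primary outcome and assigns paired t-tests to its change. Section 6.2 says the follow-up survey repeats the baseline one to see whether anything has changed. This stands. A reader of section 8.2 alone might infer that objective (i) is tested nowhere, but the document as a whole does not support that. The defect is a contradiction between two stated plans.

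A second objection concerns Table 2. A secondary sub-heading may have been lost in extraction, and section 8.2 expressly calls motivation, quality of life and social networks secondary. A reader might infer six primary tests at 0.05 each, with a correspondingly large chance of a false positive. No section plans six such tests. The sixth row, overall experience, is an impact evaluation that does not lend itself to a comparison with a pre-intervention value. No error rate for six outcomes should therefore be attached to this plan. Table 2 matters only as a third label that needs to agree with the others.

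A third objection is that error control is commonly left to the statistical analysis plan, and that the protocol states no rule by which success on either outcome alone would suffice. This also stands: the missing adjustment is not itself the fault. It needs stating only if two primaries are kept and either could carry the claim. If both had to succeed, no split of alpha would be needed.

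What survives is the conflict between the Summary with section 3.1 on one side and section 8.2 on the other. A later analysis plan could not follow both.

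**Conclusion.** The point holds as an internal contradiction that should be settled before analysis. The Summary and section 8.2 differ on whether awareness is primary and on whether its change is tested. Followed literally, section 8.2 leaves one of the two Study 1 primary objectives, and hypothesis 2 with it, without a test or an estimate of change. This conclusion rests on the text and on the fact that a rank correlation is unaffected by a uniform shift; it needs no numerical assumption.

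The multiplicity part is conditional and smaller. The 9.8% applies only if both outcomes are primary, either alone supports a claim, no adjustment is made and the tests are independent. The two outcomes come from the same participants, so independence is an assumption. With 375 completers and two-sided tests, a split to 0.025 costs 0.183 − 0.168 = 0.015 SD of the change in detectable effect.

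**What to change.** Use one outcome hierarchy in the Summary, Table 2 and section 8.2. The simplest is the one already in the Summary and section 3.1: change in brain health risk profile and change in dementia awareness as the two primaries. Then:

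- add to section 8.2 a paired pre-post comparison of the awareness score, with the mean change and its 95% CI;
- remove awareness from the list of secondary outcomes in section 8.2;
- label the other four Table 2 rows (motivation, quality of life, social networks, overall experience) as secondary;
- keep the nonparametric correlations as exploratory;
- if either primary alone could support a claim of success, state the error control, for example Holm or 0.025 each; if both must succeed, say so.

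Keeping the risk profile as sole primary, in line with section 8.1, is also defensible. The Summary and section 3.1 would then have to change, and awareness would still need its own paired comparison in section 8.2.

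The cost is protocol wording. Sections 6.2 and 7 already provide for the same measures at both time points, so no new data are needed. If alpha is split, the detectable effect grows by the small amount shown in the working.

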**Study 2**

Interview data that are obtained in the semi-structured interviews will be analysed qualitatively for content and themes that emerge, and coded and categorised using N Vivo software. Qualitative data analysis will involve an initial open coding of all transcriptions, followed by axial coding using grounded theory techniques whereby initial codes, indicators and concepts are triangulated with other findings (e.g., observational, and quantitative) leading to refined analytical levels, relevant to the study aims.

**Study 3**

Descriptive data will be compared between the groups using a two-sample t test and the Fisher exact test for continuous and categorical variables, respectively. Summary statistics will be calculated individually for the Virtual Reality Cognitive Screener, traditional cognitive assessment and questionnaire-dependent feedback scores. Younger and older adults (and older adults with cognitive impairment) cognitive performance on all measures will be compared using the two-sample t tests.

Performance scores will be analysed at each task level, given a total score, and compared between the older cognitive-intact and younger groups using the methods described above, as appropriate. Correlation between performance scores and other variables will assessed using Pearson correlation. A logistic regression will performed based on the total performance scores, followed by ROC analysis to assess its predictive capability to discriminate between cognitively intact and cognitively impaired individuals. Analyses will be performed using SPSS V22.0.

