**Planned Sample Size**

Study 1 500 community-dwelling older adults residing in NSW

Study 2 40 older adults from Study 1 participants

Study 3 100 older adults (aged 65+) and 100 young adults (aged 18+)

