**Study 2**

Based on a power analysis for biserial correlation using G*Power 3 with a conservative medium effect of ρ = .30 [47]report very high effect sizes with a similar design), and 80% power, an N of 64 is required to detect an association at p = .05 for each group. The final proposed sample size (N=100 per group) was larger than required for the present study to account for potential drop-outs between assessments.

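### The Study 3 logistic/ROC analysis has no age restriction, so the 100 young adults could enter as easy intact controls and raise the AUC above its value in older adults, for whom the aim is stated

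*Protocol*

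**What the plan says.** Section 8.2 (Study 3) treats its analyses unevenly. The t tests are split into younger adults, older adults and older adults with impairment, and task-level scores are compared between intact older adults and younger adults. The correlation follows with no group named: "Correlation between performance scores and other variables will assessed using Pearson correlation". The discrimination analysis is a logistic regression on the total score, "followed by ROC analysis to assess its predictive capability to discriminate between cognitively intact and cognitively impaired individuals", again with no age limit, stratum or age covariate. The Analysis plan in the Summary is no more specific: "Correlational analyses and receiver operating curve (ROC) will be conducted for performance scores on the virtual reality assessment module".

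Other sections bear on who is meant:

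- **Towards older adults.** The Brain Bootcamp part of section 1.1 places the screener's discriminant validity in a subset of older adults. Section 4.1 ties it to assessing cognition in older adults.
- **Towards everyone.** Hypothesis 4 (section 2) and the second Study 3 objective (section 3) speak of participants without an age limit. Section 6.5 enrols adults from age 18. Section 6.6 gives both assessments to younger and older adults alike, and section 7 uses the TICS-M to classify cognitive status without limiting this to older adults.

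Section 8.1, in a block headed Study 2 whose content belongs to Study 3, sizes the correlation by group: "an N of 64 is required to detect an association at p = .05 for each group". It does not mention the ROC.

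**The concern.** An ROC analysis compares impaired cases with intact controls. Dementia is an exclusion criterion for Study 3, so the impaired cases may be few and would be expected among the older participants. If young adults join the controls, each comparison of an impaired older adult with a young adult reflects age as well as impairment. With 10 impaired older adults, young people would make up 100 of 190 controls (53%), and the AUC would depend heavily on how well the screener separates young from old.

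The stake is the second Study 3 objective. A pooled AUC could be read as evidence that the screener detects impairment in older adults when part or all of it comes from the age difference. Section 8.2 fixes the method for this objective but does not tie it to the population named in sections 1.1 and 4.1.

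**Working it through.** **The plan's own figure.** Section 8.1 reports a "power analysis for biserial correlation using G*Power 3 with a conservative medium effect of ρ = .30", with 80% power and α = 0.05, giving 64 per group. In the point-biserial model the test is a noncentral t with df = N − 2 and noncentrality ρ√N/√(1 − ρ²). At N = 64 this is 0.30 × 8/√0.91 = 2.516, and one-sided power is 80.05%. So 64 reproduces exactly as a one-sided calculation; two-sided, 82 would be needed. At the planned 100 per group, before dropout, power is 93.0% one-sided and 87.6% two-sided. A correlation within each age group is therefore affordable. No figure in the protocol sizes the ROC.

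**Inputs for the AUC check.**
- From the protocol: 100 older and 100 young adults.
- Assumed, because the protocol gives none of them: the number impaired among the older adults, m (10 to 30); the age gap on the screener in within-group SDs, g (0.5 to 1.5, young scoring higher); all young adults classed intact; normal scores with equal SD.

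**Formulas.** Let δ be the gap between intact and impaired older adults, in SDs.
- Older adults only: AUC_old = Φ(δ/√2).
- Impaired older adults against young adults: AUC_young = Φ((δ + g)/√2).
- Pooled: the average over controls, [(100 − m) × AUC_old + 100 × AUC_young] / (200 − m).

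**True older-adult AUC of 0.70, m = 10.** Here δ = 0.742.
- g = 0.5: AUC_young = Φ(1.242/1.414) = 0.810. Pooled = (90 × 0.70 + 100 × 0.810)/190 = 0.758.
- g = 1.0: AUC_young = Φ(1.742/1.414) = 0.891. Pooled = (63 + 89.1)/190 = 0.80.

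**True older-adult AUC of 0.60, m = 10, g = 1.0.** Here δ = 0.358 and AUC_young = Φ(1.358/1.414) = 0.832. Pooled = (54 + 83.2)/190 = 0.72.

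**No discrimination in older adults (AUC 0.50, δ = 0).** Pooled AUC:

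| Impaired of 100 | g = 0.5 | g = 1.0 | g = 1.5 |
| --- | --- | --- | --- |
| 10 | 0.573 | 0.637 | 0.687 |
| 20 | 0.577 | 0.645 | 0.698 |
| 30 | 0.581 | 0.653 | 0.709 |

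With g = 0 the two component AUCs are equal and pooling does no harm. The inflation comes entirely from the age gap.

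**Correlation, for completeness.** With equal groups, the same gap g on both tests and within-group correlation w, pooled r = (w + g²/4)/(1 + g²/4). For w = 0 this gives 0.06 at g = 0.5 and 0.20 at g = 1.0. In 4,000 simulated studies of 100 + 100 people, the pooled test was significant in about 14% and 82% respectively.

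**The case against.** The strongest reply is that the protocol never says the groups are pooled. Section 8.2 uses the impaired and intact labels for subsets of the older group and treats the younger adults as a separate comparator, so the ROC sentence can fairly be read as referring to the two older subgroups. Sections 1.1 and 4.1 support that reading. Analysis populations are often left to a statistical analysis plan, and Study 3 is a feasibility study of an unvalidated screener. Section 1.1 also suggests that VR memory testing may be fairer across ages, so a gap of 1 SD on the screener cannot be presumed.

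Much of this stands. A reader might infer that section 8.2 is written for all participants together; the documents do not support that, because the text names no population. A reader might also infer that a pooled correlation will manufacture validity. Section 8.1 points the other way: it sizes the association by group and adds "The final proposed sample size (N=100 per group) was larger than required for the present study to account for potential drop-outs between assessments", while the first Study 3 objective concerns older adults. The correlation therefore needs only a clarifying phrase.

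The reply does not dispose of the ROC. The per-group sizing in section 8.1 concerns a correlation and is silent on the ROC. The issue is also more than detail deferred to a later plan, because the protocol's own statements differ: the aim is for older adults, while the hypothesis and objective are for participants in a study open from age 18 in which young adults also receive the classifying test. An analyst could follow section 8.2 to the letter and include them.

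**Conclusion.** The point holds for the logistic/ROC analysis: its population is left open in a way that conflicts with the aim stated in sections 1.1 and 4.1, and including young adults would overstate discrimination in older adults. With 10 of 100 older adults impaired, the overstatement from a true 0.70 is about 0.06 at a gap of 0.5 SD and about 0.10 at 1 SD. From a true 0.50 it ranges from 0.07 to 0.21 over gaps of 0.5 to 1.5 SD and 10 to 30 impaired.

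These sizes are conditional. They rest on assumed age gaps, an assumed number impaired, normal scores with equal SD, and all young adults being classed intact. That last assumption cannot be confirmed from the TICS-M bands in section 7, which give no label to scores above 20 and up to 40. The direction needs only that young adults count as intact and score higher on the screener. For the correlation, the point is one of alignment between sections 8.1 and 8.2. This should be corrected before analysis; it does not call the design into question.

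**What to change.** In section 8.2 (Study 3):

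1. State that the logistic regression and ROC analysis of intact versus impaired status use participants aged 65 or over only, and that young adults contribute only to the age-group comparisons.
2. As a minor alignment with section 8.1, state that the screener–TICS-M correlations are computed separately in the younger and older groups.
3. Make hypothesis 4, the second Study 3 objective and the Summary's Analysis plan name the same population.

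This changes wording only and needs no new data or recruitment. The cost is that the AUC will be lower and less precise, resting on about 100 older adults before dropout, but it will describe the population the aim names.

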# 9. QUALITY CONTROL AND ASSURANCE

### 9.1. CONTROL OF DATA CONSISTENCY

Data analysis will be undertaken using appropriate statistical programming software (e.g. SPSS) and user-written code will be saved in a shared location to enable replication and version control. Transcribed interviews will be redacted and identifiable information removed before qualitative analysis and coding. We will conduct appropriate data cleaning, harmonisation, standardisation and internal consistency checks.

